**Methods:**

This 1:1 randomised controlled trial will enrol 260 participants with subthreshold depression randomizing into 2 groups (online exercise intervention versus usual care control). The intervention consists of twice-weekly 1-h exercise online classes over 12 weeks, which will be led by certified instructors. Data will be collected at baseline (T0), immediate post intervention (T1), 3-month post intervention (T2) and 9-month post intervention (T3). The primary outcome is depressive symptoms measured by the Chinese version of Beck Depression Inventory-II (BDI-II) at T1. Secondary outcomes include anxiety symptoms, quality of life, physical activity levels, feasibility and acceptability, medication use and health service utilization, and cost assessment. Intention-to-treat analysis will be performed.

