## Methods

### Study design

This will be a pragmatic randomized controlled trial with two arms: online instructor-led exercise intervention versus usual care control in primary care. Assessments will be conducted at baseline (T0), immediate post intervention (T1), 3-month post intervention (T2) and 9-month post intervention (T3). An overview of the study design is shown in Fig. 1.

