### Data collection

Demographic information, including gender, age, education level, marital status and household income, will be collected at T0. All outcomes will be measured at T0, T1, T2 and T3 (Fig. 1). The primary and secondary outcome measures are described in details below:

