##### Medication use and health service utilization

All medications associated with an intention to improve mood or mood-related symptoms will be recorded at follow-up. These include anticonvulsants, antidepressants and anxiolytics including benzodiazepines. Utilization of health services including visits to primary care doctors (both private and public) or accident and emergency units, visits to any specialist outpatient clinics, use of other psychiatric services such as psychologists, social workers or occupational therapists, and hospitalizations will be recorded at all visits to see whether there are changes between groups on health services utilization. The electronic patient records of the Hospital Authority for the utilization of public healthcare services will be checked, supplemented by the participants’ self-report.

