##### Cost assessment

Costs using both provider and societal perspectives will be collected. The cost of healthcare service, the productivity loss of the participants and cost of caregiver will be self-reported by the participants. The cost of productivity loss of the participants will be estimated by the number of sick leave and the cost of each working days. The frequency of utilizing healthcare service and the cost of each visit including medication and transportation fee will be recorded. The cost of caregiver will be the money and time spent on taking care of the participants by caregivers. The cost of the online exercise intervention includes hiring cost of physical trainers, other administrative costs associated with the operation of the online exercise intervention programme, and costs of purchasing and maintaining the wearable trackers. The data from cost assessment will be used with the BDI-II and SF-12 scores for evaluating the cost-effectiveness of the online exercise programme.

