### Statistical analysis

Baseline characteristics of the two groups will be compared using chi-square test for categorical variables and independent samples t-test for continuous variables. Analysis of covariance (ANCOVA) for the BDI-II score at T1 will be conducted as the primary analysis, with the BDI-II score at T0 and other characteristics with significant between-group difference at T0 as covariates in the model for sensitivity analyses. Effect size estimates will be obtained for the primary outcome, with the between group effect sizes (Cohen’s d) being calculated using the mean differences from baseline and the SDs of the two groups at each time point. For the secondary analysis, linear mixed models (LMM) with random intercept will be applied to investigate the significant changes over time, for both primary and secondary outcome measures. The LMM approach is in line with the intention-to-treat principle, to include all subjects for the analysis and use all available data to assess the treatment effect over time. Maximum likelihood estimation (MLE) will be employed to handle missing data in the analyses with LMMs. A sensitivity analysis will be conducted using imputed data generated by multiple imputation. Furthermore, compliance with prescribed exercises will be added into the models to explore if this is predictor of changes in health outcomes.

In the cost-utility analysis, utility will be measured with quality adjusted life years (QALYs) based on SF-12 using the Hong Kong weights. The area under curve approach will be used to calculate the utilities at follow-ups after adjusting for baseline utility. In the cost-effectiveness analysis, remission of depressive symptoms (BDI-II score of < 14) will be used as outcome. Using both provider and societal perspectives, incremental cost-effectiveness ratio (ICER) will be calculated by dividing cost difference of two groups by between-group effect difference. We will use bootstrapping technique to assess the uncertainty of the ICER estimate. Due to the lack of a local willingness-to-pay threshold, we will generate cost-effectiveness acceptability curves to evaluate the probability of cost-effectiveness of the proposed intervention.

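### One linear random-intercept model is fixed for all repeated outcomes: a poor fit for medication use and service-use counts, and too narrow at T3 on the continuous scales if correlation falls with time

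*Protocol article*

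**What the plan says.** Under Statistical analysis, the protocol article makes ANCOVA of BDI-II at T1 the primary analysis. It then says that "linear mixed models (LMM) with random intercept will be applied to investigate the significant changes over time, for both primary and secondary outcome measures". Maximum likelihood in these models is to handle missing data. The section names no residual covariance structure, robust standard error, logistic model or count model.

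The Abstract lists what counts as secondary: "Secondary outcomes include anxiety symptoms, quality of life, physical activity levels, feasibility and acceptability, medication use and health service utilization, and cost assessment". On medication, the section on medication use and health service utilization says "All medications associated with an intention to improve mood or mood-related symptoms will be recorded at follow-up", without stating whether the outcome is any use, a number of drugs or a dose. On service use, the same section says that visits, admissions and other contacts "will be recorded at all visits to see whether there are changes between groups on health services utilization", so a between-group comparison is intended. Cost assessment gives the unit: "The frequency of utilizing healthcare service and the cost of each visit including medication and transportation fee will be recorded".

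Data collection says "All outcomes will be measured at T0, T1, T2 and T3". Study design places T1 at the end of the 12-week programme, and T2 and T3 three and nine months after that. The four occasions therefore lie at about 0, 3, 6 and 12 months, with gaps of about 3, 3 and 6 months.

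**The concern.** Two features of the prescribed model are doubtful.

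**Type of outcome.** Visits and admissions are counts, usually with many zeros and with a variance that rises with the mean. Medication use, if analysed as any use, has a variance that depends on its prevalence. The exclusion criteria under Participants rule out current antidepressant use, so use of that class should be about zero at T0 and can only rise. A linear model with one residual variance for all visits does not describe such data.

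**Correlation structure.** A random intercept with independent residuals gives every pair of visits the same correlation, whether they are three or twelve months apart. If closer visits are in fact more alike, the model spreads one average error over all contrasts. Early contrasts then look less precise than they are, and late ones more precise.

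At stake are the intervals and p-values of the secondary follow-up analyses, above all at T3, where the article would look for a lasting effect. Bonferroni correction of those analyses does not repair a standard error that is too small. The plan also relies on likelihood to deal with dropout, and that argument depends on the covariance model being adequate.

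**Working it through.** **The plan's own figure.** The article gives no figure for the mixed model. Its sample size reproduces. The pooled SD is sqrt((8.35² + 9.52²)/2) = 8.95. A two-sided t-test for 3.5 points at 80% power needs 103.6, so 104 per arm, and 104/0.80 = 130. This rests on the T1 comparison, so nothing below changes it.

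**Inputs.** Visit times of 0, 3, 6 and 12 months come from Study design. Correlations are assumptions, because the article gives none. The calculation takes equal variances, complete data and a separate mean for each arm at each visit. The contrast is the between-arm difference in change from T0.

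**Formula.** With unit variance, the true variance of a change from T0 to visit k is proportional to 2(1 − r0k). The random-intercept model uses 2(1 − r̄) for every k, where r̄ is the mean of the six pairwise correlations. Hence

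- SE ratio (model/true) = sqrt((1 − r̄)/(1 − r0k))
- actual type I error = 2(1 − Φ(1.96 × ratio))

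**Worked case: correlation 0.7 per 3 months, decaying exponentially.** The six correlations are 0.700 (T0–T1), 0.490 (T0–T2), 0.240 (T0–T3), 0.700 (T1–T2), 0.343 (T1–T3) and 0.490 (T2–T3), so r̄ = 0.494.

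- T1: sqrt(0.506/0.300) = 1.30, type I error 0.011
- T2: sqrt(0.506/0.510) = 1.00, type I error 0.051
- T3: sqrt(0.506/0.760) = 0.82, type I error 0.110

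**Range of assumed patterns** (SE ratio, then type I error at nominal 0.05):

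| Correlation pattern | T1 | T2 | T3 |
|---|---|---|---|
| Equal, 0.6 | 1.00, 0.050 | 1.00, 0.050 | 1.00, 0.050 |
| Linear, 0.6 at 3 months to 0.5 at 12 | 1.05, 0.040 | 1.01, 0.049 | 0.94, 0.066 |
| Linear, 0.7 to 0.3 | 1.23, 0.016 | 1.03, 0.044 | 0.81, 0.114 |
| Exponential, 0.5 per 3 months | 1.20, 0.019 | 0.98, 0.055 | 0.88, 0.086 |
| Exponential, 0.9 per 3 months | 1.41, 0.006 | 1.02, 0.045 | 0.76, 0.136 |

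An unstructured covariance has ratio 1 in every row.

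**Bonferroni.** In the worked case, the T3 error at nominal 0.05 is 0.110/0.05 = 2.2 times nominal. For eight tests (an assumed number) the threshold is 0.05/8 = 0.00625. The actual error is then 2(1 − Φ(2.734 × 0.816)) = 0.026, about 4 times nominal.

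**Medication use and counts.** These were simulated with no treatment effect, 104 per arm and latent correlation 0.7 or 0.8 per 3 months. All rates are assumed.

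| Outcome | Type I error at T1 | Type I error at T3 |
|---|---|---|
| Any use, about 0% or 2% at T0, then 3%, 5%, 8% | 0.004–0.006 | 0.064–0.092 |
| Any use, 10% at every visit | 0.025–0.028 | 0.068–0.079 |
| Negative-binomial count, mean 2 at every visit | 0.007–0.015 | 0.099–0.127 |
| Negative-binomial count, means 1, 1, 1, 2 (longer window before T3) | 0.001 | 0.120–0.123 |

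The third row lies close to the continuous result for the same decay (T3 0.110 and 0.123 for 0.7 and 0.8). So most of the distortion comes from unequal correlation and variance over visits, not from non-normality as such.

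**The case against.** The strongest reply is that the sentence is shorthand for the repeated scale scores. Recruitment, attendance and the evaluation form cannot enter an arm-by-visit model, and costs have their own bootstrap. The secondary efficacy hypotheses name only anxiety and quality of life. A correlated residual could also sit on top of the random intercept, and an analysis plan could say so. Part of this stands: the sentence cannot literally cover every item listed as secondary. But the article compares service use between groups, names no other model for it, and states a random intercept and nothing further. Reading in an exception or a residual structure adds words that are not there.

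The size also depends on how baseline enters the model, which the article does not say for the mixed model. With T0 as a covariate with visit-specific slopes, the residual variances in the worked case are 1 − r0k² = 0.510, 0.760 and 0.942, with mean 0.737. The T3 ratio is then sqrt(0.737/0.942) = 0.885, with type I error 0.083 instead of 0.110. The fault becomes smaller but keeps its direction.

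A linear model for a difference in mean counts can be a defensible target with about 104 per arm, provided its standard errors are sound. That stands, and it is why robust standard errors are an acceptable alternative for the continuous scores and why the rate-ratio summary of a count model is partly a choice.

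A reader might go further and infer that the error bars are wrong throughout, that medication is a yes/no outcome, or that use of all mood medication is near zero at entry. The documents support none of these. The errors are conditional on the correlation pattern. The medication scale is undefined. The entry exclusion covers antidepressants only, whereas the outcome also counts anticonvulsants and anxiolytics, whose users are not excluded as such.

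**Conclusion.** The point holds in a limited form. The article fixes one linear random-intercept model without exception by outcome type. That is a poor choice for medication use and service-use frequencies. For the continuous scales it rests on equal correlation between unequally spaced visits.

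If correlation falls with time, T1 contrasts are conservative, T2 contrasts are about right (ratio 0.98 to 1.03), and T3 contrasts are too liberal, with type I error of about 0.07 to 0.14 at nominal 0.05. These figures rest on assumed correlations, complete balanced data and a change-from-T0 contrast; dropout was not simulated. With constant correlation and variance there is no error.

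The primary ANCOVA, the sample size and the ICER bootstrap are untouched, and the article calls the secondary analyses exploratory. The importance is therefore moderate: the plan should be changed, but the main conclusion of the trial does not hang on it.

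**What to change.** - Limit the linear mixed model to the continuous scores: BDI-II, BAI, SF-12 and any continuous IPAQ-SF score. Use categorical arm-by-visit effects and an unstructured within-person covariance, or robust standard errors.
- Define the medication outcome. Analyse any use at the follow-up visits with a logistic mixed model or GEE.
- Analyse visit and admission counts with a negative-binomial model, with follow-up time as offset.

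Data collection and sample size do not change. The cost is revised wording and minor programming. An unstructured covariance has 10 parameters (4 variances and 6 covariances) instead of 2, which 260 participants can support. Counts would be summarised as a rate ratio and not as a difference in means.

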### Sample size

From a previous trial on assessing the efficacy of group-based behavioural activation with mindfulness for treating subthreshold depression in primary care in Hong Kong, mean (standard deviation) of BDI-II score at baseline for intervention and usual group were 19.18 (8.35) and 17.68 (9.52) respectively among participants with subthreshold depression. Pooled mean and standard deviation were 18.43 and 8.95 from two groups. For moderate baseline severity, the minimum clinically important difference (MCID) on the BDI-II was estimated at 3.5 points [24]. Assuming at least the MCID could be seen in the online exercise programme at 4-month post randomisation compared to usual care, sample size of 104 each group achieve 80% power to detect the difference of 3.5 points in BDI-II with a common standard deviation of 8.95 at a significance level of 0.05 using two-sided t-test. The corresponding effect size of 0.39 is similar to the finding from a systematic review that physical activity is beneficial for improving depressive symptoms with effect size of 0.43 [8]. From our experience in running online exercise intervention for people with subthreshold depression, a dropout rate of 13% at 12 month follow up was observed. To be conservative, we assume drop out to be 20%, and set our enrolment target at participants in total of 260 with 130 participants in each group.

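### The clinical cost-effectiveness analysis uses only a yes/no BDI-II cut, with no baseline adjustment described; adjusting remission for T0 BDI-II and adding a cost per BDI-II point would gain precision at almost no cost (minor)

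*Protocol article*

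**What the plan says.** Two places in the protocol article describe the clinical effect measure for the economic evaluation.

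- Cost assessment: "The data from cost assessment will be used with the BDI-II and SF-12 scores for evaluating the cost-effectiveness of the online exercise programme".
- Statistical analysis: "In the cost-effectiveness analysis, remission of depressive symptoms (BDI-II score of < 14) will be used as outcome". The ICER is the cost difference divided by the difference in effect between the two groups. Its uncertainty is assessed by bootstrap, and acceptability curves are planned because there is no local willingness-to-pay threshold.

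The Statistical analysis section also plans a separate cost-utility analysis on SF-12 QALYs, for which it does state adjustment for baseline utility. It states no corresponding adjustment for remission, and no ICER per BDI-II point appears anywhere.

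The Sample size section works on the full scale: "sample size of 104 each group achieve 80% power to detect the difference of 3.5 points in BDI-II with a common standard deviation of 8.95". The test behind this figure is a t-test, two-sided at 5%. The primary analysis is an ANCOVA of the BDI-II score at T1.

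**The concern.** Cutting a 21-item score at 14 discards information. A fall from 19 to 15 counts as no effect, and a fall from 14 to 13 counts as full success. The incremental effect is the denominator of the ICER, so a noisier effect term puts more bootstrap replicates near or below zero effect and flattens the acceptability curve. Leaving out T0 BDI-II, which is already collected and usually correlates with follow-up, wastes more.

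Cost-effectiveness is a stated secondary objective and hypothesis. At stake is a trial that shows a BDI-II benefit while its clinical cost-effectiveness analysis, on the same data, has an inconclusive effect term.

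**Working it through.** **Inputs from the Sample size section.** Difference 3.5; SD 8.95; 104 evaluable per arm; two-sided alpha 0.05; "Pooled mean and standard deviation were 18.43 and 8.95 from two groups".

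**Assumptions added here.** The usual-care mean at follow-up is 18.43 (the document gives it only as an earlier trial's baseline mean), so the exercise mean is 18.43 - 3.5 = 14.93. The SD is common. The shape is normal or gamma. The T0-T1 correlation is 0.5. The article gives no time point for remission; the planned 3.5-point difference is used.

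**Step 1: reproduce the plan.** SE of the mean difference = 8.95 x sqrt(2/104) = 1.241, and z = 3.5/1.241 = 2.82. The noncentral t power at 104 per arm is 80.1%, and 104/0.80 = 130 per arm. Both agree with the article.

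**Step 2: unadjusted cut, normal shape.**
- Usual care: Phi((14 - 18.43)/8.95) = 31.0%.
- Exercise: Phi((14 - 14.93)/8.95) = 45.9%.
- Difference 0.148; SE = sqrt((0.310 x 0.690 + 0.459 x 0.541)/104) = 0.0667; z = 2.22.
- Relative information = (2.22/2.82)^2 = 0.62. The relative SE rises by 1/sqrt(0.62) = 1.27.
- Power (pooled two-proportion z-test) 59.5%; 168 per arm would be needed for 80%.
- 95% CI half-width as a share of the effect: 1.96/2.22 = 88%, against 1.96/2.82 = 70% for the score.
- Over usual-care means of 11 to 20 and cuts of 14 or 13.5, relative information is 0.58 to 0.64.

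**Step 3: unadjusted cut, gamma shape, same means and SD.** Shape = (mean/SD)^2 and scale = SD^2/mean: 4.24 and 4.35 for usual care, 2.78 and 5.37 for exercise.
- P(score < 14) = 35.4% v 53.8%; difference 0.184; SE = sqrt((0.354 x 0.646 + 0.538 x 0.462)/104) = 0.0677; z = 2.72.
- Relative information = (2.72/2.82)^2 = 0.93; power about 77%.
- Over usual-care means of 16.5 to 20.5 and cuts of 14 or 13.5: relative information 0.85 to 0.97, power about 73% to 78%.

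**Step 4: add the baseline (correlation 0.5).** For the score, SE falls to 1.241 x sqrt(1 - 0.25) = 1.075, so z = 3.26 and power is about 90% by normal approximation. Simulation with integer scores clipped to 0-63 gives:

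| Effect measure | Normal | Gamma |
|---|---|---|
| Score, T0-adjusted | 89% | 89% |
| Remission, unadjusted | 59-61% | 77-79% |
| Remission, T0-adjusted | about 67% | 83-85% |

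The ranges cover separate simulation runs. Adjusting remission for T0 BDI-II recovers about 6 to 8 points. With both measures adjusted, the remaining gap is 89 - 67 = 22 points (normal) or 4 to 6 points (gamma).

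**Step 5: the acceptability curve.** This needs cost variance, which the article does not give. As an illustration only (normal shape, no baseline adjustment), assume a mean cost difference of 3000, a cost SD of 2000 to 20000 and a threshold of 1.5 to 3 times the ICER. The probability of cost-effectiveness is then 0.67 to 0.93 with remission and 0.68 to 0.97 with the score. The gap is 1 to 5 points and is smallest at the largest cost SD.

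**The case against.** - **Shape.** A reader might infer a flat loss of about 40% of the information. The documents do not support that. Nothing says BDI-II is normal, the scale is bounded at zero, and the SD is about half the mean. Under a gamma shape the unadjusted loss is 3% to 15%. This stands, so both shapes must be reported.
- **Mixed comparisons.** Setting an adjusted score against unadjusted remission combines two issues. The article does not say that remission will be analysed unadjusted, and a condensed article may leave this to the full plan. The like-for-like gaps in Step 4 are the fair ones. The text does state baseline adjustment for utility, however, so saying the same for remission is reasonable.
- **Scope.** A reader might infer that the whole economic evaluation is weakened. It is not: the SF-12 QALY analysis is not dichotomised. The ANCOVA and the mixed models keep the continuous BDI-II.
- **Contradiction.** A reader might see the Cost assessment and Statistical analysis sections as conflicting. Remission is derived from the BDI-II score just as QALYs are derived from SF-12, so the later section can be read as specifying the earlier one.
- **Interpretability.** Cost per remission is a different quantity from cost per point and is easier for policy makers to read. Without a local threshold, that matters. It is a legitimate choice, and the documents give no ground for removing it as an outcome.
- **Power.** No power is claimed for the economic analyses. That lowers the severity, but does not justify discarding precision that is free.

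**Conclusion.** The concern holds as a minor efficiency point. The BDI-II-based cost-effectiveness analysis uses only a cut score and describes no baseline adjustment, although the full score and T0 BDI-II are both available. The unadjusted cut keeps about 62% of the effect-term information on a normal shape and about 85% to 97% on a gamma shape. After adjusting both measures at an assumed correlation of 0.5, the score still has more power: 89% against about 67% (normal) or 83% to 85% (gamma).

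These figures concern the effect term of one ICER. They rest on the assumed follow-up mean, shape and correlation. The effect on the acceptability curve cannot be fixed from the documents and is modest in the range illustrated.

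**What to change.** In the Statistical analysis section:

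1. Keep cost per remission (BDI-II < 14), but state that the remission difference is estimated adjusting for continuous T0 BDI-II, for example by logistic regression with standardisation, refitted within each bootstrap replicate.
2. Add beside it an ICER and acceptability curve per BDI-II point, using the T0-adjusted mean difference. This also makes the link to the Cost assessment section explicit.

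No new data are needed. The cost is a sentence or two of wording, one more model inside the planned bootstrap, and a second, less intuitive effect unit to report.

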### Participants

The following inclusion and exclusion criteria will be used to determine the eligibility of the participants.

The inclusion criteria are: (1) aged 18 years or above; and (2) having subthreshold depression as defined by having a score 5–9 on the Patient Health Questionnaire depression scale (PHQ-9) [18], i.e., having a total score of 5 to 9 inclusive.

The exclusion criteria are: (1) dysthymia with subthreshold depressive symptoms that last for 2 years or more; (2) major depression within the past 6 months; (3) lifetime history of other psychiatric disorders (including but not limited to generalized anxiety disorder, schizophrenia, bipolar affective disorder and substance use disorder); (4) current use of antidepressant; (5) currently enrolled in any form of psychological interventions for any depressive symptoms; (6) medical illness with a prognosis of less than 6 months to live; and (7) recently diagnosed or uncontrolled cardiovascular, metabolic or neurological conditions.

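### The cost-effectiveness outcome called remission (BDI-II below 14) has no baseline condition; on the planning figures about three in ten participants would already meet it at entry

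*Protocol article*

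**What the plan says.** Under Statistical analysis, the protocol article fixes the effect measure of the cost-effectiveness analysis: "remission of depressive symptoms (BDI-II score of < 14) will be used as outcome". The ICER is the cost difference between the groups divided by the difference in effect, with bootstrapping for uncertainty. In the same paragraph the cost-utility analysis adjusts for utility at baseline. No such adjustment is stated for remission.

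Under Participants, the symptom criterion for entry is the PHQ-9 alone, "having a total score of 5 to 9 inclusive". No BDI-II threshold appears among the inclusion or exclusion criteria, and BDI-II is not a stratification factor under Randomization, concealment and blindness. Data collection places all outcomes, and so BDI-II, at T0 as well as at every follow-up.

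Under Sample size, the expected baseline comes from a previous local trial in subthreshold depression: "mean (standard deviation) of BDI-II score at baseline for intervention and usual group were 19.18 (8.35) and 17.68 (9.52) respectively". The article then states: "Pooled mean and standard deviation were 18.43 and 8.95 from two groups".

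**The concern.** Remission ordinarily means passing from above a cut-off to below it. As the outcome is written, a participant who scores 10 at T0 and 10 at follow-up is a remission. Entry and outcome use different instruments, so nothing in the design keeps such people out, and the planning figures suggest they are not rare.

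Cost-effectiveness is both a stated objective and a stated hypothesis. A policy reader given a cost per remission will take it as the price of one person moved out of depressive symptoms. If a large part of the count was never above the cut-off, the number means something else. In addition, T0 status predicts follow-up status, so an unadjusted comparison lets a chance difference in T0 status between the arms into the denominator of the ICER.

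**Working it through.** **Inputs from the article (Sample size).** Source-arm baselines 19.18 (SD 8.35) and 17.68 (SD 9.52); pooled 18.43 and 8.95; difference 3.5 points; 104 per group for 80% power at two-sided 0.05; 20% dropout; 130 per group, 260 in total.

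**Reproducing the plan's own figures.**
- Pooled mean, giving the arms equal weight: (19.18 + 17.68)/2 = 18.43. Pooled SD: √((8.35² + 9.52²)/2) = 8.954.
- The two-sample t-test needs 103.6, so 104 per group (power 80.1%); 104/0.80 = 130 per group, 260 in total. All agree with the article.

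**Share below 14 at T0.** The article gives no such figure, so a distributional shape has to be assumed.
- Normal, cut at 14: Φ((14 − 18.43)/8.95) = Φ(−0.495) = 0.310, or 80.7 of 260.
- Normal, cut at 13.5 because scores are whole numbers: Φ((13.5 − 18.43)/8.95) = Φ(−0.551) = 0.291, or 75.6 of 260.
- Zero-truncated normal, gamma, lognormal and negative binomial shapes with parameters from the same mean and SD: 0.278 to 0.357.
- Source arms separately, normal: 0.248 to 0.268 for 19.18 (8.35) and 0.330 to 0.350 for 17.68 (9.52).
- Extremes over all shapes and arms: 0.241 to 0.417.

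**What the outcome would show at the planned effect.** Assume normality, an unchanged SD, no mean change in controls and a mean 3.5 points lower with the intervention (18.43 − 3.5 = 14.93). With the cut at 13.5, the proportion below 14 is 29.1% in control and Φ((13.5 − 14.93)/8.95) = 43.7% with the intervention, a difference of 14.6 points. With the cut at 14 the figures are 31.0%, 45.9% and 14.9.

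**Who makes up the count.** This depends on the T0-to-follow-up correlation, which the article does not give. A bivariate normal simulation over an assumed range, cut at 13.5, gave:

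| Assumed correlation | Control, started below 14: % below at follow-up | Control, started at 14 or above: % below at follow-up | Effect, all | Effect, started at 14 or above | Effect, started below 14 |
|---|---|---|---|---|---|
| 0.3 | 41.8 | 23.8 | 14.6 | 14.0 | 16.1 |
| 0.5 | 51.4 | 19.9 | 14.6 | 13.7 | 16.7 |
| 0.7 | 63.0 | 15.3 | 14.5 | 13.6 | 16.7 |

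The share of control-arm remissions already below 14 at entry is 0.291 × 0.418/0.290 = 42% at correlation 0.3, and 0.291 × 0.630/0.291 = 63% at 0.7. In the intervention arm it is 0.291 × 0.578/0.436 = 39% and 0.291 × 0.797/0.436 = 53%.

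**Chance imbalance.** The standard error of the between-arm difference in the share below 14 at T0 is √(2 × 0.31 × 0.69/130) = 0.057, or 5.7 points. The part that reaches follow-up is this times the gap between the first two result columns: 5.7 × (0.418 − 0.238) = 1.0 point at correlation 0.3, and 5.7 × (0.630 − 0.153) = 2.7 points at 0.7. With the cost difference held fixed, a one-standard-error imbalance against the intervention multiplies the ICER by 14.6/13.6 = 1.07 at correlation 0.3, or by 14.6/11.9 = 1.23 at 0.7. In its favour the factors are 14.6/15.6 = 0.94 and 14.6/17.3 = 0.84.

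**The case against.** The article gives the economic analysis one paragraph. The analysis set, time point and covariates of a secondary economic outcome may well stand in a fuller document, and T0 BDI-II is collected, so nothing prevents a baseline condition. That is fair, and it limits the point to what the article does fix: the name and the cut-off, for a population admitted without a BDI-II floor.

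Three stronger readings are tempting, and the document supports none of them.

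- *Those below 14 at entry count as successes whatever the treatment does.* They do not. A person who rises to 14 or more stops counting, and in the illustration 37% to 58% of controls who start below 14 do so (100 − 63.0 and 100 − 41.8). Keeping people below the cut-off is a benefit in its own right in a trial whose Discussion speaks of prevention.
- *The ICER is biased.* Under 1:1 randomisation the share below 14 at T0 is equal in expectation and cancels in the difference. Only chance imbalance remains.
- *The effect is diluted by people who cannot remit.* The intervention is delivered to, and paid for in, everyone randomised, so the ratio over all randomised participants is a coherent intention-to-treat quantity. Dilution appears if each person simply drops 3.5 points: 14.9 points over all, against 0.149/0.69 = 22 points among those starting at 14 or above. With correlations of 0.3 to 0.7 it disappears, and those starting below 14 show a slightly larger effect than the rest.

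A restriction to T0 BDI-II of 14 or above is therefore a trade-off rather than a correction. It drops about 30% of participants and any preventive effect, and it uses a subgroup that was not stratified.

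**Conclusion.** The point holds as one of meaning and of unadjusted chance imbalance, on a secondary outcome. As written, the outcome labels as remission people who were never above the cut-off. On the planning mean and SD that status applies at entry to roughly three in ten participants: 29% to 31% under a normal shape, about 24% to 42% across the other shapes and the two source arms. The figure rests on an assumed shape and on a previous trial's baseline, and this trial's sample may differ. None of the shapes tried makes the share negligible.

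A one-standard-error imbalance in T0 status is about 5.7 points, of which some 1 to 3 points would reach an illustrative effect of about 15 under the assumed correlations. The primary analysis and the QALY analysis are untouched. The change is worth making because it is nearly free and the present label would mislead users of the ICER.

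**What to change.** In the economic analysis, keep all randomised participants and define the effect as the between-group difference in the proportion with BDI-II below 14 at follow-up, reported under that name. Adjust the difference for T0 BDI-II, for example by a logistic model with T0 BDI-II as a continuous covariate, averaged over all participants to give a difference in proportions. Refit it in every bootstrap resample, with each participant's costs and outcome resampled together.

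Remission proper (T0 BDI-II of 14 or above and follow-up below 14) may be added as a supplementary analysis. Its costs must come from the same subset. It would use about 179 to 184 of 260 participants on the normal-shape figures and have a wider interval, and it should not replace the all-randomised analysis.

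The cost is one or two sentences in the plan and a model fit inside the bootstrap. No new data are needed. What is given up is the shorter label, cost per remission, for the main ratio.
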